## Abstract

**Background:**

Fatigue is a multifactorial condition that leads to disease and loss in production, and it affects a large number of workers worldwide. This study aims to demonstrate a resistance exercise protocol that individuals will perform during the work schedule, and to evaluate the effectiveness of this exercises program for fatigue control.

**Methods/Design:**

This is a cluster randomized controlled trial with two arms and is assessor blinded. A total of 352 workers of both sexes, aged 18–65 years, from a medium-sized dairy plant were enrolled in this study. Participants will be recruited from 13 production sectors according to the eligibility criteria and will be randomized by clusters to either the Progressive Resistance Exercise (PRE) intervention group or the Compensatory Workplace Exercise (CWE) comparative group. A resistance exercise program will be implemented for both groups. The groups will receive instructions on self-management, breaks, adjustments to workstations, and the benefits of physical exercise. The PRE group will perform resistance exercises with gradual loads in an exercise room, and the CWE group will perform exercise at their workstations using elastic bands. The exercise sessions will be held 3 times a week for 20 min. The primary outcome measures will be symptoms of physical and mental fatigue, and muscular fatigue based on a one-repetition maximum (1RM). The secondary outcome measures will be level of physical activity, musculoskeletal symptoms, physical condition, perceived exposure, and productivity. The workers will be assessed at baseline and after a 4-month program. A linear mixed model will be applied on an intention-to-treat basis.

**Discussion:**

This intervention is expected to reduce symptoms of fatigue in the workers. The exercise program is indicating in the workplace, although there are few studies describing the effects of exercise on the control of fatigue in the workplace. Emphasis will be placed on adherence to the program, which may result in significant and clinically important reductions in fatigue. It is also expected that the findings of this study will contribute significantly to the decision-making capacity of professionals working in the field of occupational health.

**Trial registration:**

U.S. National Institutes of Health, ClinicalTrials.gov Identifier: NCT02172053. Date registered 19 June 2014.

## Background

Fatigue is a nonspecific symptom associated with chronic health problems and functional deterioration at work. It is complex and multidimensional and varies in intensity depending on the imposed overload [1–9]. Workplace fatigue is a common complaint that requires attention due to its high prevalence and its association with serious dysfunctions among workers [5]. It affects physical and mental health [3, 9], increasing the chance of accidents and musculoskeletal complaints [10], and reducing performance and productivity [4].

The symptoms of fatigue are due to individual characteristics [5, 6] as well as to work factors involving physical and mental demands, such as lack of planning with regard to work activities, rosters, and work shifts; environmental conditions; and standing for long periods [9]. Factors related to fatigue outside the workplace are sedentary behavior, lifestyle, and unhealthy diet, all of which build up over time [9]. Fatigue can be mental, due to prolonged periods of high cognitive demands along with the physical activity imposed by the daily load of highly physical jobs [7, 9]. Acute fatigue is a normal phenomenon in healthy workers and it is reversed after a period of rest [2]; however, chronic fatigue is more severe and often cannot be reversed simply by reducing workloads or resting [3, 6, 8]. The effects of fatigue on worker health and job performance can be short term or long term [2, 3, 6]. The short-term effects are reduced attention span, poor decision-making, reduced alertness, and poor control of emotions [3]. Fatigue can also increase the rate of mistakes, reduce reaction times, and elevate the likelihood of accidents and injuries [11]. The long-term effects are heart disease, diabetes, high blood pressure, gastrointestinal disorders, sleep loss, depression, and anxiety [2].

Fatigue contributes to the occurrence of musculoskeletal disorders, which represent a major problem for the health of workers worldwide [4, 5]. Workplace characteristics, repetitive tasks, static contractions, and inadequate posture are associated with the majority of structural disorders and the development of fatigue [10]. Various organizational aspects of work have been associated with a variety of adverse health effects, especially occupational disorders such as fatigue [10]. Thus, it becomes crucial to adopt measures for evaluating and managing these organic dysfunctions manifested as the development of fatigue [7]. Exercise programs have been widely used for fatigue management and pain relief, and to improve muscle strength, flexibility, and cardiovascular conditioning [12–15].

Exercise has been shown to have highly beneficial effects on physical and mental health [16], promoting significant changes to lifestyle and wellbeing [17]. It has a great impact on the health of all individuals, reducing mortality rates and increasing life expectancy [12, 13], as well as improving function in the musculoskeletal, blood, cardiopulmonary, immune, and nervous systems [12, 18]. Furthermore, it can reduce many of the risk factors for non-communicable chronic diseases (hypertension, cholesterol levels, diabetes), as well as percentage of body fat and body mass index [18, 19].

Exercise at the workplace has positive effects on the health of workers and is most effective when done in a group because there is more motivation thus increasing adherence to the program [20]. There is strong evidence of the effectiveness of strength training at the workplace for reducing musculoskeletal complaints in specific regions of the body [20–24]. A variety of strength training protocols are described in the literature, including protocols to decrease pain in the cervical, lumbar, and shoulder areas; low-intensity training; high-intensity training with concentric contractions; high-intensity training with isometric contractions; and highly intensive training (HIT) [20–22, 25]. However, there is consensus that resistance exercises are more effective [20, 25], and 20-min training sessions [20–25] 3 times a week for periods of 10 weeks or more [20, 23] reduce musculoskeletal complaints in the workplace. The protocol of heavy resistance exercise at the workplace includes exercise with higher intensity in eccentric and concentric contractions, using dumbbells, elastic bands, and exercises against gravity [20]. The effectiveness of medium- and long-term progressive resistance exercise programs with progressive loads for muscle strength gain and fatigue reduction has already been shown in the literature [18, 21], with most studies being cross-sectional in nature. In contrast, the small number of longitudinal studies that describe the benefits of resistance training for fatigue management in the workplace hinders decision-making regarding interventions for this population. Therefore, the advantage of this study is its randomized clinical trial design in the occupational context, with control of all of the variables that simulate the gym environment.

The hypothesis investigated in this study is that the physical load, high work demand, and absence of breaks imposed on production workers can contribute to an increase in the need for recovery due to increased symptoms of fatigue. It is understood that improving the workers’ physical conditioning is essential to managing the symptoms of fatigue at the workplace. To achieve that, resistance training with progressive loads is the most effective program.

Thus, our objective in this study is demonstrate a resistance exercise protocol to be performed at the workplace during the work schedule, and to describe the procedure that will be used to evaluate the effectiveness of this program in fatigue management for industrial workers.

## Methods

### Study design, approval, and registration

This is a cluster randomized controlled trial (RCT) two-arm (parallel group) with double blinded (investigator and assessor). The study protocol was approved by the Institutional Research Ethics Committee (Approval Number: 454709) according to the Helsinki Declaration as revised in 2013. Previously registered at ClinicalTrials.gov under protocol number NCT02172053. This protocol was reported according to SPIRIT guidelines.

### Setting and study sample

The study will include workers of both sexes, aged 18–65 years, recruited from production lines in a medium-sized dairy plant located in the state of Espírito Santo, Brazil. Workers exposed to moderate to high levels of biomechanical and cognitive demands who meet the eligibility criteria will be invited to participate. All information about the study design is in Fig. 1.

**Fig. 1 Fig1:**
[figure not shown]
Flowchart of participants recruitment and study design

### Eligibility criteria

The dairy plant has 600 employees among its administrative and production sectors. The study will focus on the production sector, which enrolled 352 workers. The inclusion criteria will be as follows: permanent employment status, fixed work shifts, agreement to participate, and signing the informed consent form. The exclusion criteria will be temporary employment status, vacation, or sick leave to ensure group comparability, the feasibility of the interventions, and blinding.

### Randomization

Prior to clustering according to exposure level, 13 of the plant’s production sectors will be included in the study: Boilers, Processing, Receiving/Cooling/Standardization, Milk, Butter, Cheese, Milk Caramel, Yoghurt, UHT Plant, Milk Powder, Stock, and Warehouse. Allocation will be performed on Research Randomizer (https://www.randomizer.org/) by a researcher not involved with the data collection.

### Blinding

Due to the nature of the intervention, it is not possible to blind the workers and physical therapists who carry out the interventions. However, the researchers who will conduct the interviews and assessments will be blinded (double blinded). After the assessment, the blinding will be tested by having the researchers guess the type of intervention the worker received: Progressive Resistance Exercise (PRE) intervention group or the Compensatory Workplace Exercise (CWE) and write it down.

### Intervention protocols

Workers from both groups will receive initial instructions on health management (impact of fatigue, management of work demands, rest breaks, set up of workstations) and the importance of exercise to promote health and lifestyle changes. After the implementation of the exercise programs, these guidelines will be reinforced daily throughout the intervention period.

### Progressive Resistance Exercise (PRE) - intervention group

Workers allocated to this training program will perform light warm-up and stretching exercises followed by specific training with resistance and strength exercises. The training program of the PRE group will focus on muscle resistance, starting at 30% of the one-repetition maximum (1RM) [26]. The speed of the exercise will be moderate to allow control of the angle of movement. Load increase will be progressive according to each worker’s adaptability and physiological characteristics. Training will follow the principles of resistance training, starting with the adaptation to load phase (microcycle) and progressing to the load incorporation phase (mesocycle) and the training phase (macrocycle) [26]. The following muscle groups will be trained: elbow flexors, elbow extensors, trunk flexors, trunk extensors, knee flexors, knee extensors, thigh adductors, thigh abductors, and ankle dorsal and plantar flexors.

All exercises will be carried out in 3 sets of 10 repetitions with a 30-s interval between sets. The training will be held at the workplace in a room equipped with dumbbells, ankle weights, weight plates, and bars.

### Compensatory Workplace Exercise (CWE) – comparative group

Participants in this training program will have a light workout-involving warm-up and stretching exercises and resistance training with elastic bands in groups at their workstations. The protocol includes training of the following muscle groups: elbow flexors, elbow extensors, trunk flexors, trunk extensors, knee flexors, knee extensors, thigh adductors, thigh abductors, and ankle dorsal and plantar flexors. All exercises will be carried out in 3 sets of 10 repetitions with a 30-s interval between sets.

### Supervision and training schedule

Interventions will take place over a period of 4 months, beginning in August 2016. The outcomes will be assessed at baseline, and there will be a follow-up at the end of the intervention. Both groups of participants will train for 20 min, 3 times a week on alternate days. All interventions will be carried out during working hours at the workplace, totaling 1 h per week. All exercise protocols developed for this study are shown in Appendix I.

Ten experts will be involved in the research and will receive 12 h of training on the protocol and objectives of the study, regardless of their role (assessors, instructors, or lecturers). The researcher will supervise the training sessions at the workplace. Heart rate and blood pressure will be measured before every session. If any significant change that could hinder training is identified in any vital signs, the participant will be sent to the company’s outpatient clinic for assessment.

### Outcome measures

The primary outcome measures will be perception of fatigue and the secondary outcome measures will be musculoskeletal complaints and pain, quality of life, level of physical activity, physical condition, perceived exposure to risk factors, and productivity. The data collection instruments for these outcomes are described below. All outcomes will be evaluated at baseline and after 4 months (at the end program).

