### Primary outcome measures

#### Perception of fatigue

The symptoms of fatigue attributed to work-related physical, organizational, and psychosocial demands and stress will be evaluated using the Need for Recovery Scale (Br-NFR) [30–32]. This Likert-type scale has 11 questions with 4 possible responses (0 = never; 1 = sometimes; 2 = often; and 3 = always). The answer “always” indicates an unfavorable situation and receives 3 points, except for item 4, which has a reversed score. The total score is obtained by adding all of the scores and converting them into a scale ranging from 0 (lowest) to 100 (maximum) by means of a simple rule of three [32]. In this case, the higher the score is, the greater the number of symptoms and the greater the need for recovery.

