#### Muscular fatigue

Muscular fatigue will be evaluated using the 1RM test, which is the maximum amount of weight that can be lifted one time while performing a standardized exercise. The test will be completed when the individual 1RM reference value is found. The one-repetition maximum will be tested in the following muscle groups: biceps, triceps, deltoid, quadriceps femoris, hamstrings, and triceps surae, using an appropriate load for the individual’s fitness level.

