#### Physical fitness assessment

Postural assessment - static assessment to identify postural changes with asymmetry that may affect training. This assessment will be carried out by direct observation and recorded on a specific form.Vital signs - heart rate, respiratory rate, lung auscultation, blood pressure, and oxygen saturation. These signs will be assessed using a heart monitor (POLAR - RS800CX), a fingertip pulse oximeter, a stethoscope, and a sphygmomanometer. The aim is to monitor the individual before, during, and after exercise.Body Mass Index (BMI) - a widely used parameter to estimate an individual’s health according to their weight and height. The World Health Organization (WHO) uses this index as an indicator of obesity levels in different countries. It is calculated by dividing the weight (kg) by the height squared (meters).Waist-Hip Ratio (WHR) and Waist Circumference - WHR is an excellent way to identify the existence of increased risk for cardiovascular disease. Scientific studies have shown that a high concentration of abdominal fat (near the heart), without even considering the degree of obesity, is a risk factor for the development of heart disease [37]. The following equation will be used to measure WHR: waist measurement divided by hip measurement (W ÷ H). The higher the values are, the higher the risk. Results greater than or equal to 0.8 for women and 1.0 for men indicate a high risk for cardiovascular disease. Waist circumference is a measure that helps identify the people most likely to suffer from cardiovascular diseases [38] and it is as important as the BMI. A circumference greater than or equal to 94 cm in men and 80 cm in women is an indicator of a 3.25 times higher risk of developing heart disease [38]. A tape measure will be used to measure waist circumferences.Body Fat Percentage - assessed with a body fat caliper commonly used in epidemiological research, outpatient clinics, doctor’s practices, and gyms. This apparatus features rulers that measure the fat in the skinfolds at different sites (triceps, biceps, pectoralis, subscapularis, midaxillary, suprailiac, abdomen, thigh, and calf). With these measurements, the professional can make a precise assessment of body composition and monitor the patient accordingly.One-Repetition Maximum (1RM) - this test evaluates muscle strength. It measures the maximum amount of weight that an individual can lift in a single repetition. The 1RM will be tested in the following muscle groups: biceps, triceps, deltoid, quadriceps femoris, hamstrings, and triceps surae using an appropriate load for the individual’s fitness level. Dumbbells, weight plates, and other conventional weights will be used for this measurement [26].Somatotype Rating - this assessment will identify the workers’ body type or physical classification. The terms endomorph (fat), mesomorph (muscular), and ectomorph (thin) will be used to describe the workers’ somatotype according to their weight, height, and body fat percentage at baseline [26].Neck Circumference (NC). This measure is indicative of the level of obesity. A very large neck circumference may be related to increased risk of heart disease and metabolic disorders. A neck circumference ≥ 37 cm for men and ≥ 34 cm for women is equivalent to a BMI ≥ 25 kg/m^2^. A neck circumference ≥ 39.5 cm for men and ≥ 36.5 for women is equivalent to a BMI ≥ 30 kg/m^2^. A neck circumference of up to 37 cm in men and up to 34 cm in women indicates a normal BMI [39]

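### 1RM is given conflicting roles and labels: a primary outcome called muscular fatigue in two places, left out of the primary outcome in a third, and a secondary strength measure in a fourth

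*Protocol article*

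**What the plan says.** Four places in the protocol article bear on the rank and meaning of 1RM.

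- **Abstract, Methods/Design:** "The primary outcome measures will be symptoms of physical and mental fatigue, and muscular fatigue based on a one-repetition maximum (1RM"). Here 1RM is primary.
- **Outcome measures, opening paragraph:** "The primary outcome measures will be perception of fatigue and the secondary outcome measures will be musculoskeletal complaints and pain, quality of life". The list goes on to include physical condition among the secondaries. 1RM is not named as primary.
- **Primary outcome measures:** two subsections. Fatigue perception "will be evaluated using the Need for Recovery Scale (Br-NFR"), which yields one total on a 0–100 scale. Then: "Muscular fatigue will be evaluated using the 1RM test, which is the maximum amount of weight that can be lifted one time". The muscles are "biceps, triceps, deltoid, quadriceps femoris, hamstrings, and triceps surae, using an appropriate load".
- **Secondary outcome measures, Physical fitness assessment:** "One-Repetition Maximum (1RM) - this test evaluates muscle strength". The six muscle groups are the same.

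Three other places matter. The PRE section sets the training load "starting at 30% of the one-repetition maximum (1RM") and then increases it. The Sample size section uses Br-NFR only. The Statistical analysis section gives one 5% significance level and no rule for combining or ordering primary outcomes.

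**The concern.** The primary outcome decides what counts as success, and here one variable is both primary and secondary. Someone reporting the trial could cite the protocol for either rank after seeing the data.

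The label adds to the problem. The trial's aim is fatigue control. If 1RM is a primary measure of fatigue, a heavier single lift in the PRE arm becomes a primary fatigue result. The PRE arm trains against progressive loads set from 1RM, so a strength gain there is plausible whatever happens to fatigue. The trial could then report a positive primary fatigue outcome while Br-NFR, the outcome behind the sample size, has not moved.

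**Working it through.** **1. Rank and label, side by side**

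| Place | Rank of 1RM | Label |
|---|---|---|
| Abstract | primary | muscular fatigue |
| Outcome measures, opening paragraph | not in the primary | none |
| Primary outcome measures | primary | muscular fatigue |
| Physical fitness assessment | secondary | muscle strength |

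The first and third rows agree in substance. The conflict is between those two and the other two.

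**2. What the test measures.** The Muscular fatigue subsection defines 1RM as the most weight lifted once. That definition includes no repeated effort and no decline in force. The fitness section says "this test evaluates muscle strength". On the protocol's own terms, 1RM measures strength.

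**3. Which outcome the sample size supports.** The stated figure is 86 per group, for a 20% difference in Br-NFR at α = 0.05, 80% power and up to 15% loss. It cannot be reproduced, because no standard deviation or baseline is given and the scale of the 20% is not stated. Back-solving gives:

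- Evaluable per group: 86 × 0.85 = 73.1, taken as 73.
- Implied standardised difference (two-sided): (1.960 + 0.842) × √(2/73) = 0.46.

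Nothing in the calculation refers to 1RM.

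**4. Conditional error rates.** These assume that any positive primary counts as success and that each is tested at 5%. The article states neither.

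- Two independent tests: 1 − 0.95² = 9.75%.
- Br-NFR plus six separate 1RM tests, all independent: 1 − 0.95⁷ = 30.2%.
- The same seven with equally correlated 1RM statistics and Br-NFR independent (simulation, 400,000 draws): 27.9%, 24.6%, 20.5%, 18.3% and 15.3% for assumed correlations of 0.3, 0.5, 0.7, 0.8 and 0.9.

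Clustering is ignored throughout.

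**5. The mislabelling itself.** Family-wise error describes the case with no true effect on anything. The concern here is a true strength effect under a fatigue label. Suppose Br-NFR has no effect and one 1RM test has an assumed power of 80% to 95%. The chance of at least one positive primary is then 1 − 0.95 × 0.20 = 81% to 1 − 0.95 × 0.05 = 95%. No alpha adjustment corrects this, because the strength effect would be real.

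**The case against.** The best defence is that the abstract and the Primary outcome measures heading agree, so the opening paragraph of Outcome measures may just be loosely worded. The Discussion also frames the expected result as fewer fatigue symptoms, and no section says that a 1RM result alone would count as success. These points are fair, but they do not remove the conflict. The fitness section still lists the same test as secondary and calls it strength. An analysis plan could not show which of these ranks the protocol had pre-specified.

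Four stronger readings are tempting, and the document does not support them.

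- **Three separate definitions of the primary outcome.** Two of the statements largely agree and both include 1RM.
- **Up to seven unadjusted tests with 21–30% family-wise error.** The article does not say that the six muscles are tested separately, that any one result suffices, or that no adjustment is made. A 1RM summary and an alpha rule may be in an analysis plan that is not shown. The figures also depend on assumed correlations and fall to about 15% at 0.9.
- **A plan to claim fatigue control from strength.** The text leaves this open but does not state it.
- **A test biased towards PRE by equipment.** 1RM is tested with dumbbells and plates, which PRE uses and the elastic-band arm does not. Familiarity favouring PRE is therefore possible, but nothing in the document demonstrates it.

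**Conclusion.** The point holds as a contradiction in rank and label. 1RM is primary in two places, absent from the primary in a third and secondary in a fourth, and it is called both fatigue and strength. This is wrong as written, not detail lost in condensing the protocol, and it should be settled before between-group results are seen. The conclusion rests on the protocol's own wording and needs no calculation.

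The consequence is that a strength gain could pass as a primary fatigue result with Br-NFR unchanged. How likely that is cannot be read from the document. The 81–95% range depends on an assumed power for 1RM and an assumed rule that any positive primary suffices. The multiplicity figures (9.75% for two independent tests; 30% for seven independent tests, or about 15–28% with correlated 1RM tests) are conditional remarks, not properties of the stated plan.

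**What to change.** Name the 4-month Br-NFR total score as the single primary outcome in the abstract, the Outcome measures paragraph and the Primary outcome measures section. This agrees with the Outcome measures paragraph and with the basis of the sample size. List 1RM once, as a secondary outcome labelled muscle strength, and state that 1RM results do not support a claim of fatigue reduction.

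Make the change as a dated amendment before between-group results are seen, since the trial is described as ongoing. The sponsor gives up one primary claim. If 1RM is a registered primary outcome (the registry record was not available for this review), removing it is an outcome change that must be justified, not a wording edit.

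If the sponsor keeps 1RM as co-primary, it should label it strength, pre-specify one 1RM summary and state the alpha rule. As an illustration of the cost, take a Bonferroni split over two tests at the implied difference of 0.46. The power for Br-NFR with 73 evaluable per group would fall from 80% to 71%. Restoring 80% would need 89 evaluable per group, or 89/0.85 = 105 enrolled, before any allowance for clustering.
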